#### Aims

The overarching aim of the present study is to implement and evaluate the long-term effectiveness & cost-effectiveness of internet-delivered interventions for depression and anxiety disorders within IAPT services. The specific research questions include the following:Are the SilverCloud *Space from Depression and Space from Anxiety* internet-delivered interventions in IAPT effective in treating depression and anxiety disorders, and maintaining outcomes at follow-up, compared to waiting-list groups?Are the SilverCloud *Space from Depression and Space from Anxiety* internet-delivered interventions cost-effective in treating depression and anxiety disorders in IAPT?Are mediators/mechanisms of change and maintenance associated with both post-treatment and long-term effectiveness of internet-delivered interventions for depression and anxiety?

We hypothesize that: a) the iCBT interventions will be more effective than the waiting-list group in treating depression and anxiety disorders; b) the iCBT interventions will be cost-effective compared to the waiting-list group in treating depression and anxiety; c) we expect that mediators/ mechanisms of change including, repetitive negative thinking styles, emotion regulation skills, therapeutic alliance, credibility and expectancy in iCBT, CBT skills usage and therapist behaviours will be identified as positively impacting post-treatment outcomes and maintenance of gains in iCBT.

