#### Mechanisms of change and maintenance

##### Scale to Assess Therapeutic Relationship – Patient version (STAR-P) [57]

This scale will be employed to assess patients’ experiences of the therapeutic relationship online. It will be administered to patients throughout treatment following each progress review with the clinician.

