##### Scale to Assess Therapeutic Relationship – Clinical version (STAR-C) [57]

This will be employed to assess clinicians’ experiences of the therapeutic relationship online. The measure will be administered each time the clinician writes a review for their clients.

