#### Dropout measure

Finally, a *dropout questionnaire* will assess participants’ reasons for dropout from treatment. It includes only one open question asking for details about the specific reasons for dropout.

The study measures and assessment times are summarised in Table 2.

**Table 2 Tab2:** Study measures and assessment times

Measure	Assessment	Time of assessment
M.I.N.I. 7.0.2 for DSM-5	Diagnosis	BL and 3-FU
PHQ-9	Depression	BL, contin, Post-T, FU
GAD-7	Anxiety	BL, contin, Post-T, FU
IAPT Phobia Scale	Specific Phobia	BL, contin, Post-T, FU
WSAS	Functioning	BL, contin, Post-T, FU
SPIN	Social Phobia	BL, Post-T, FU
HAI	Health anxiety	BL, Post-T, FU
PSWQ	GAD	BL, Post-T, FU
PDSS	Panic	BL, Post-T, FU
EQ-5D-5 L	Health status	BL, Post-T, 6-FU, 9-FU, 12-FU
ReQol-10	Recovering quality of life/ mental wellbeing	BL, Post-T, 6-FU, 9-FU, 12-FU
CSRI	Resource utilisation	BL, Post-T, 6-FU
PEQ	Patient experience	Post-T
STAR-C	Therapeutic alliance	Throughout treatment, at each review of client
STAR-P	Therapeutic alliance	Throughout treatment, after each progress review with clinician
PBRS-A	Repetitive Negative Thinking	BL, week 4, Post-T, 3-FU
ERQ	Emotion Regulation	BL, Post-T
FATS	CBT-related skills usage	FU
Therapist behaviours checklist	Therapist behaviours	During treatment at review of client
Expectancy / credibility	Expectancy and credibility with the intervention	BL, week 4, Post-T
Dropout questionnaire	Reasons for dropout	3-FU

*BL* Baseline, *Post-T* Post-Treatment, *FU* All follow-ups, *3-FU* 3-month follow-up, *6-FU* 6-month follow-up, *contin* continuous, *PHQ-9* Patient health questionnaire-9, *GAD-7* Generalized anxiety disorder-7, *WSAS* Work and social adjustment, *SPIN* Social Phobia Inventory;` *HAI* Short health anxiety inventory, *PDSS* Panic disorder severity scale-self report, *PSWQ* Penn state worry questionnaire, *EQ-5D-5 l* EuroQol-5 Dimension-5 level, ReQoL-10 Recovering quality of life – 10 item version, *CSRI* Client services receipt inventory, *PEQ* Patient Experience questionnaire, *PBSR-A* Positive Beliefs about Rumination Scale – Adapted Version, *FATS* Frequency of Actions and Thoughts Scale, *ERQ* Emotion Regulation Questionnaire

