### Statistical analysis

The effectiveness of the internet-delivered interventions compared to control will be analysed using the intention to treat (ITT) approach. Participation levels will be monitored throughout the study and reasons for withdrawal or non-compliance of study subjects will be recorded to document bias associated with non-random protocol deviations. Any potential imbalances will be reported and considered fully in interpretation of the trial results. Missing data will be evaluated for randomness and imputed using multiple imputation procedures.

Differences in baseline primary and secondary outcome measures between treatment groups and waiting list control groups will be identified using χ^2^ tests for categorical variables and ANOVAs or t-tests for continuous variables. Efficacy of treatments over time will be measured using mixed effects models. To complement the post-hoc comparisons, the magnitude of change within and between the groups on the primary and secondary outcomes measures will be established using Cohen’s *d* statistic. Bonferroni corrected *p*-values will be reported for multiple comparisons. All statistical analyses will be conducted in SPSS, SAS and R. Results will be presented following CONSORT guidelines for reporting parallel group randomised trials.

The established IAPT definitions of recovery will be used in our analysis, where ‘recovery’ is determined by patients moving from ‘caseness’ at the beginning of the intervention (i.e. scoring ≥9 on the PHQ-9 or ≥8 on the GAD-7) to ‘non-caseness’ at the end of treatment (thus scoring below the cut-off). Two further established measures will be considered: *reliable improvement*, where the patient has a significant decrease in their PHQ-9 / GAD-7 score upon completion of their course of treatment; and *reliable recovery*, where the patient meets the criteria for both recovery and reliable improvement. Thus, a patient who moves from caseness to non-caseness, and does so by showing a significant decrease in their symptom scores, is said to have a reliable recovery [44].

Exploratory analyses, including the use of correlation and multiple regression, will be conducted to explore the role that mechanisms of change and maintenance measures play in the benefits obtained from the interventions. Moderation and mediation analyses may include the use of macros for SPSS and/or bootstrapping for exploring the role that mechanisms of change play on the outcomes.

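### Hypothesis (c) claims that alliance and therapist behaviours improve outcome, but the analysis as described fixes no time order, so it cannot tell that from improvement raising alliance

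*Protocol article*

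**What the plan says.** Under Aims, hypothesis (c) expects that mechanisms including "therapeutic alliance, credibility and expectancy in iCBT, CBT skills usage and therapist behaviours will be identified as positively impacting post-treatment outcomes", and extends this to maintenance of gains. That is a directional statement about effect. Research question 3, in the same section, is weaker: "Are mediators/mechanisms of change and maintenance associated with both post-treatment and long-term effectiveness".

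Under Statistical analysis the article names the methods: "Exploratory analyses, including the use of correlation and multiple regression, will be conducted to explore the role that mechanisms of change and maintenance measures play". It then adds, with reference to outcomes: "Moderation and mediation analyses may include the use of macros for SPSS and/or bootstrapping for exploring the role that mechanisms of change play on the" […]. No covariates, lag or handling of earlier symptom change are given.

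The patient-rated alliance scale (STAR-P) is timed as follows: "It will be administered to patients throughout treatment following each progress review with the clinician". For the clinician-rated scale (STAR-C): "The measure will be administered each time the clinician writes a review for their clients". Table 2 agrees, giving for STAR-P "Throughout treatment, after each progress review with clinician". The therapist behaviours checklist is optional and offered at each communication. Support during treatment describes six reviews in which the practitioner responds to the work done. Table 2 lists PHQ-9 and GAD-7 at baseline, continuously, post-treatment and at all follow-ups.

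**The concern.** By the time alliance is rated, symptoms may already have moved. A patient who is improving may rate the relationship higher, and a practitioner may write differently to a patient who is struggling. Either would produce an association with the post-treatment score even if the rating had no effect on it. For therapist behaviours the bias can also run in reverse, making a helpful behaviour look harmful because it is used with patients who are doing badly.

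Randomisation gives no protection. The waiting list receives no treatment for 8 weeks, so in that period alliance varies only among treated patients and is not randomised.

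At stake is whether hypothesis (c) could be declared supported when it is false. The Discussion says the mechanism work may inform how interventions are tailored.

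**Working it through.** **1. Sample sizes available.** The Sample size section gives 144 per diagnosis. This reproduces: control n = (1 + 1/2)(1.96 + 0.8416)² / 0.5² = 47.1, rounded up to 48, with 96 treated; power by noncentral t is 80.2%. Then 288 × 1.25 = 360, or 120 treated per diagnosis and 240 over both. These figures only supply n here. The article gives no figure for the mechanism analyses.

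**2. Model with no alliance effect.** All correlations below are assumptions, because the documents give none.
- Baseline symptoms b have variance 1.
- Mid-treatment symptoms are m = 0.6b + 0.8e₁.
- Post-treatment symptoms are y = 0.7m + √0.51·e₂, with no alliance term.
- Alliance is A = a(b − m)/√0.8 + √(1 − a²)·e₃, so a is the correlation of alliance with earlier improvement.

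**3. Baseline-only regression, by formula.** The partial correlation of A with y given b is

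r = −a(0.8 × 0.56/√0.8) / √[(1 − 0.42²)(1 − 0.2a²)], where 0.56 = 0.7 × 0.8 and 0.42 = 0.7 × 0.6.

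At a = 0.3: r = −0.1503/√(0.8236 × 0.982) = −0.167. With n = 120, |t| ≈ 0.167 × √117/√(1 − 0.028) = 1.83 against a critical value of 1.98. Rejection is about Φ(1.83 − 1.98) = 44%. The sign favours the hypothesis: higher alliance goes with a lower score. Given m, y does not depend on A, so a regression that also includes m has a true coefficient of zero.

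**4. Simulation.** n = 120, 3,000 runs, two-sided 0.05, true alliance effect zero. Entries are rejection rates.

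| a | Correlation with post score | Correlation with change | Regression, baseline only | Regression, baseline + earlier symptoms | Same, symptom reliability 0.89 |
|---|---|---|---|---|---|
| 0 | 5.2% | 5.1% | 5.1% | 4.8% | 4.3% |
| 0.2 | 10.0% | 32.8% | 21.6% | 4.7% | 5.6% |
| 0.3 | 17.9% | 63.0% | 43.9% | 6.0% | 6.1% |
| 0.5 | 40.7% | 97.9% | 88.2% | 5.4% | 8.7% |

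The first four result columns assume symptoms measured without error. At n = 96 the baseline-only regression rejects 18.1%, 36.8% and 80.7% for a = 0.2, 0.3 and 0.5; at n = 240 it rejects 38.6%, 73.1% and 99.4%. The largest rate with earlier symptoms included is 11.2% (n = 240, a = 0.5, reliability 0.89).

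**5. Repeated-review version.** Here six reviews are simulated, and alliance equals a person trait plus c times the improvement so far plus noise, again with no effect on symptoms. The week-8 score is regressed on mean alliance and baseline.
- For c = 0.15, 0.3 and 0.5, rejection is 16.1%, 46.7% and 85.0% at n = 96, and 26.7%, 76.7% and 98.9% at n = 192.
- A lagged model adjusted for the current score stays between 4.1% and 7.2%.
- If alliance follows true rather than recorded symptoms (c = 0.3), baseline-only against lagged is 19.0% against 14.2% (n = 96) and 38.2% against 32.5% (n = 192).
- A repeat run of that last case gave 20–26% falling to 15–19%, and 39–49% falling to 31–36%.

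**The case against.** The strongest reply is that the article does not exclude the right analysis. What a regression coefficient tests depends on its covariates, and none are named. A model that adjusts for symptoms before the rating is still multiple regression, and covariates and lags may be set out in a full protocol or analysis plan that is not shown. This stands. A reader might infer that correlation and regression as such can only test for association, or that the trial has committed itself to a baseline-only model. The documents support neither.

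Second, the analyses are labelled exploratory and research question 3 asks only about association, which these methods answer. This also stands, but hypothesis (c) goes further, and the exploratory label does not remove a directional bias.

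Third, moderation and mediation analyses are also named. They do not rescue alliance: a product-of-coefficients mediation uses the same regression of outcome on alliance, and untreated controls have no alliance to measure.

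Fourth, the remedy is imperfect. If alliance tracks true symptoms, the lagged model removes only part of the inflation. Table 2 does not say how the continuous symptom scores line up with reviews, and checklist data may be sparse. All of this stands and should be stated with the fix.

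**Conclusion.** The point holds in a limited form. Hypothesis (c) is causal and directional, and goes beyond both research question 3 and the exploratory analyses as described. For measures taken at reviews, neither a correlation with outcome or change nor a regression that omits symptoms before the rating can separate an effect of alliance from an effect of improvement on alliance.

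The direction of the problem follows from the design. Its size does not: the rejection rates rest on assumed symptom correlations and feedback strengths, and stay near 5% if there is no feedback. The primary PHQ-9 and GAD-7 comparisons are not touched. The point is worth correcting because a published hypothesis could otherwise be reported as supported on evidence that does not bear on it.

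**What to change.** In Statistical analysis, for STAR-P, STAR-C and the behaviours checklist:
- Specify a time-ordered regression: the mechanism score at a review predicts the next PHQ-9 or GAD-7, adjusted for baseline and for scores recorded up to that review, with clustering by participant.
- Report the reverse lag (symptom score predicting the next mechanism score) beside it.
- State that simple correlations with post-treatment outcome are descriptive and do not support hypothesis (c).
- Under Aims, reword (c) as association wherever only association is tested, in line with research question 3.
- State the limits: residual confounding by unmeasured symptom change, possibly sparse and selective checklist data, and no answer from this model on maintenance of gains.

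The cost is wording, some extra analysis, and work to align the continuous symptom scores with review dates. No new measure has to be scheduled. Fewer positive mechanism findings should be expected.

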**Methods:**

The study is a parallel-groups, randomised controlled trial examining the effectiveness and cost-effectiveness of iCBT interventions for depression and anxiety disorders, against a waitlist control group. The iCBT treatments are of 8 weeks duration and will be supported by regular post-session feedback by Psychological Wellbeing Practitioners. Assessments will be conducted at baseline, during, and at the end of the 8-week treatment and at 3, 6, 9, and 12-month follow-up. A diagnostic interview will be employed at baseline and 3-month follow-up. Participants in the waitlist control group will complete measures at baseline and week 8, at which point they will receive access to the treatment. All adult users of the Berkshire NHS Trust IAPT Talking Therapies Step 2 services will be approached to participate and measured against set eligibility criteria. Primary outcome measures will assess anxiety and depressive symptoms using the GAD-7 and PHQ-9, respectively. Secondary outcome measures will allow for the evaluation of long-term outcomes, mediators and moderators of outcome, and cost-effectiveness of treatment. Analysis will be conducted on a per protocol and intention-to-treat basis.

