Resource-use and subsequent costs will be estimated over the 12-month time horizon for the intervention group and for the 8-week waiting list time period for the control group. Healthcare resource will be valued using unit costs derived from available data sources [62–66].

For the purpose of the economic evaluation, EQ-5D-5 L and ReQoL-10 preference-based tariff score values will be used to elicit the quality adjusted life year (QALY) using the area under the curve (AUC) method to account for the collection of this data at multiple time points between baseline and 12-month follow-up in both trial-arms. The proposed economic analysis will be conducted for those with anxiety and those with depression separately and as a whole patient group. All economic analysis will be performed using Stata version 14 (or an updated version). Due to the shorter time horizon of the control groups (8 weeks based on a waiting list approach) compared to the intervention group (12 months with outcome assessment at 8 weeks, 6 months, 9 months and 12 months), methodological work will be carried out to assess the feasibility and uncertainty around extrapolating outcomes from the 8-week time period in the control group to a longer time horizon (e.g. 6-months, 9-months and 12-months) using survival analysis methods [67]. Cost per QALY analysis will be carried out over multiple time horizons (e.g. 8-weeks, 6-months, 9-months and 12-months) to address the uncertainty around decision making from using observed data (up to 8 weeks) and extrapolated outcomes (beyond 8 weeks) for the economic evaluation. Incremental mean point estimates of the difference in cost and QALYs between trial groups will be used to determine the incremental cost effectiveness ratio (ICER). ICER is defined here as the ratio between incremental costs and incremental effectiveness and the following formula will be employed:$$ ICER=\frac{\mathrm{Cost}\kern0.5em \mathrm{active}\kern0.5em \mathrm{intervention}\kern0.5em \mathrm{group}\hbox{-} \mathrm{Cost}\kern0.5em \mathrm{control}\kern0.5em \mathrm{intervention}\kern0.5em \mathrm{group}}{\mathrm{Efectiveness}\kern0.5em \mathrm{or}\kern0.5em \mathrm{Utility}\kern0.5em \mathrm{active}\kern0.5em \mathrm{intervention}\kern0.5em \mathrm{group}\kern0.5em \hbox{-} \mathrm{Efectivenes}\kern0.5em \mathrm{or}\kern0.5em \mathrm{Utility}\kern0.5em \mathrm{control}\kern0.5em \mathrm{intervention}\kern0.5em \mathrm{group}}. $$

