Statistical bootstrapping will be used to plot the cost-effectiveness acceptability curves (CEACs) for the purpose of describing the probability of cost-effectiveness of the intervention compared to usual care at willingness-to-pay thresholds normally used by decision makers (i.e. £20,000 per QALY). One-way sensitivity analysis will be used to describe the uncertainty around these estimates. If the trial results suggest there is considerable uncertainty around the cost-effectiveness of the intervention, a simple economic decision model will be designed to inform an expected value of information (EVI) analysis. These EVI results can be used to suggest the upper bound cost of future research around this area of care.

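### Beyond 8 weeks the cost-per-QALY analysis has no matched control cost, and the named extrapolation method has no defined event

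*Protocol article*

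**What the plan says.** All of the economic text is in the protocol article, Statistical analysis.

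- **Costs.** "Resource-use and subsequent costs will be estimated over the 12-month time horizon for the intervention group and for the 8-week waiting list time period". The second, shorter window is that of the controls.
- **Horizons.** "Cost per QALY analysis will be carried out over multiple time horizons (e.g. 8-weeks, 6-months, 9-months and 12-months". The ICER is the between-group difference in mean cost divided by the difference in mean QALYs.
- **Control arm after week 8.** "methodological work will be carried out to assess the feasibility and uncertainty around extrapolating outcomes from the 8-week time period in the control group". The target horizons are 6, 9 and 12 months, and the method is given as "using survival analysis methods [67" (the number is a literature citation). Costs are not mentioned in this step.
- **QALYs.** These are areas under the EQ-5D-5L and ReQoL-10 utility curves, to account for "collection of this data at multiple time points between baseline and 12-month follow-up in both trial-arms".
- **Comparator.** The acceptability curves are to show the "probability of cost-effectiveness of the intervention compared to usual care".

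The abstract's Methods paragraph says: "Participants in the waitlist control group will complete measures at baseline and week 8, at which point they will receive access to the treatment". The section Waiting list control group confirms that these participants are untreated for 8 weeks and then start treatment.

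**The concern.** An ICER compares like with like only if costs and QALYs in both arms cover the same period. The text sets a 12-month cost window for one arm and an 8-week window for the other, then plans ICERs at horizons where the shorter window is not enough. It foresees filling the gap for outcomes but does not say what control cost enters the numerator.

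The method named for the extrapolation models time to an event. Each untreated control contributes two utility scores, and the economic text defines no event or time-to-event variable from which an area-under-the-curve QALY would follow.

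Long-term cost-effectiveness is part of the overarching aim, and cost-effectiveness against the waiting list is hypothesis (b) under Aims. The 6-, 9- and 12-month results therefore carry weight, and an analyst following the printed text could not compute them on a matched basis.

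**Working it through.** The economic section states no cost, QALY or ICER value, so there is no plan figure to reproduce. The check sets the passages side by side and then does the horizon arithmetic.

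**1. What is available in each arm**

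| Item | Intervention | Untreated control |
|---|---|---|
| Cost window (Statistical analysis) | 12 months | 8 weeks |
| Utility scores (Table 2; abstract, Methods) | baseline, post-treatment, 6, 9, 12 months | baseline, week 8 |
| Named extrapolation | not needed | outcomes only |

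At 8 weeks both arms have observed costs and utilities. After week 8 the control arm has neither while untreated, and any later score would come from someone who has begun iCBT. The statement that utilities run to 12 months in both arms cannot stand beside the 8-week control horizon given in the same paragraph.

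**2. Does outcomes include costs?** The paragraph gives resource use and costs their own sentence and their own horizon. The outcome assessment dates it lists for the intervention group (8 weeks, 6, 9 and 12 months) match the post-baseline schedule of the utility measures in Table 2. They do not match the CSRI, which is scheduled at baseline, post-treatment and 6 months only. The more natural reading is that costs are not included, but no sentence excludes them.

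**3. Size of the gap**

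For a horizon of H weeks, write C_T and C_W for mean intervention and waiting-list cost.

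- Matched numerator: C_T(0 to H) − C_W(0 to H)
- Literal numerator: C_T(0 to H) − C_W(0 to 8)
- Literal minus matched: C_W(8 to H), which cannot be negative

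The literal reading therefore overstates incremental cost, against the intervention. The share of the control period without a costing rule is (H − 8)/H:

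- 6 months (26 weeks): 18/26 = 69.2%
- 9 months (39 weeks): 31/39 = 79.5%
- 12 months (52 weeks): 44/52 = 84.6%

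**4. Illustration in money (assumed costs)**

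Assume an equal background care cost in both arms of £200 to £2,000 per person-year. The overstatement at 12 months is:

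- £200 × 44/52 = £169; £169/£20,000 = 0.0085 QALY
- £2,000 × 44/52 = £1,692; £1,692/£20,000 = 0.085 QALY

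Assume also a true incremental cost of £100 and a gain of 0.02 QALY. The matched ICER is 100/0.02 = £5,000. The literal ICER is (100 + 169.23)/0.02 = £13,462 at the low end and (100 + 1,692.31)/0.02 = £89,615 at the high end. With a gain of 0.05 QALY, the matched £2,000 becomes £5,385 to £35,846. Under these assumptions the literal result can fall on either side of the £20,000 threshold that the protocol cites.

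**The case against.** The section recognises the unequal horizons itself and gives them as the reason for the extrapolation work. It lists a matched 8-week analysis, separates observed from extrapolated results, and adds one-way sensitivity analysis and a possible decision model. A cost-per-QALY analysis at a given horizon arguably implies both arms at that horizon, and a health-economics plan that is not shown may supply the control costs.

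Much of this stands, and it rules out four stronger readings that a reader might infer:

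- *That the trial's ICER is simply 12-month cost minus 8-week cost.* Several horizons are planned and the 8-week one is sound. The defect is confined to the later ones.
- *That control costs are deliberately excluded from extrapolation.* The wording omits them; it does not rule them out. The extrapolation itself is framed as a study of feasibility and uncertainty, not as a settled analysis.
- *That survival methods cannot apply.* The cited reference is not at hand, and a derived event is conceivable, for example loss of caseness as used in the recovery definition. What the documents support is that no event is named.
- *That the error would manufacture cost-effectiveness, or that results would be presented throughout as a comparison with usual care.* The literal subtraction works against the intervention, and the waiting list is named as comparator in the abstract, Aims and Trial design.

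What the objection does not answer: the longer-horizon analyses are stated as a commitment, and the article itself fixes the two cost windows. The inconsistency is therefore in the printed text and is not merely detail left to another document.

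**Conclusion.** The point holds for horizons beyond 8 weeks. As written, the incremental cost at 6, 9 and 12 months has no matched control cost. The direction of the literal reading is certain as long as controls incur any cost after week 8. Its size cannot be derived from the documents, and the pound figures above rest entirely on assumed costs and effects. The extrapolation method is underspecified because no event is defined for a utility-based QALY. Two wording errors go with it: 12-month utility collection in both arms contradicts the 8-week control horizon, and usual care mislabels an untreated waiting list. The clinical primary outcomes, randomisation and sample size are not affected.

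**What to change.** 1. State that every ICER uses the same window for costs and QALYs in both arms.
2. Make the observed 8-week ICER the base case.
3. Present the 6-, 9- and 12-month results as scenario analyses that extrapolate both control costs and control utilities under named assumptions, such as the week-8 value held or convergence to the iCBT mean.
4. Either define the event that the survival methods would model and how it yields a QALY, or replace them with a utility-trajectory model or the simple decision model already foreseen.
5. Correct the phrase on data collection in both trial arms, and replace usual care with waiting list.

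The cost is a change of wording in the protocol or health-economics plan and a few scenario runs; no new data are needed for the base case. The price in interpretation is that the long-term ICER is reported as a scenario and not as a trial estimate.
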